### Allocation concealment mechanism

Upon confirmation of eligibility (patients must meet all inclusion criteria and must not meet exclusion criteria), the clinical site will contact a centralized internet randomization system (https://randomizer.at/). Patients will be randomized using block randomization to one of the two arms, MAD arm or CMOA arm.

Generation of allocation sequence, enrolment of participants, and assignment of participants to interventions will be performed by authors in the Department of Sleep Medicine, DMIMS (DU).

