### Study design (Fig. 1, Table 1)

The present study is a randomized, controlled, parallel, and two-armed (i.e., MAD and CMOA), clinical trial. The duration of the study will be for one year. The patients reporting to the Department of Sleep Medicine, which are diagnosed cases of moderate OSA will be considered as participants for this study.

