**Assessments:**				
Primary outcome			X	
Secondary outcomes				X

The study involves 40 sample sizes. At 80% power of the study, the minimum sample size calculated for each group is 16. However, 20 samples in each group will be selected to minimize errors and to cover any loss of cases during follow-up.

These 40 participants will be randomized by creating a computer-generated randomization list. Participants will be assigned random numbers based on consecutive enrolment into group 1 or a control group subjected to MAD (*n*=20) and another group, i.e., group 2 subjected to CMOA.

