### Investigations

#### Polysomnography (PSG)

An overnight PSG will be performed in the Department of sleep medicine before and after one month and three months of intervention by MAD and CMOA. Recording of PSG will be scored as per the guidelines of the American Academy of Sleep Medicine. The event of apnea or hypopnea per hour will be calculated.

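### The concealment section relies on a central internet system yet gives sequence generation, enrolment and assignment to the same department's authors, so concealment is not secured as written

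*Protocol article*

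**What the plan says.** The protocol article describes allocation in two places.

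- **Allocation concealment mechanism, first paragraph.** After a patient is found to meet every inclusion criterion and no exclusion criterion, "the clinical site will contact a centralized internet randomization system". The method is blocked: "Patients will be randomized using block randomization to one of the two arms, MAD arm or CMOA arm". No block size is given.
- **Allocation concealment mechanism, second paragraph.** "Generation of allocation sequence, enrolment of participants, and assignment of participants to interventions will be performed by authors in the Department of Sleep Medicine".
- **Study design, text below Table 1.** "These 40 participants will be randomized by creating a computer-generated randomization list", and then "Participants will be assigned random numbers based on consecutive enrolment into group 1 or a control group". Neither the internet system nor blocking is mentioned here.

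Two other statements give context. Patients come from the same department (Study design): "The patients reporting to the Department of Sleep Medicine, which are diagnosed cases of moderate OSA will be considered as participants". The sleep studies are done there too (Polysomnography): "An overnight PSG will be performed in the Department of sleep medicine before and after one month and three months of intervention". The recordings are scored to a named professional standard. The article does not say who scores them, and it mentions no masking of any role.

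**The concern.** Concealment requires that whoever decides on a patient's entry cannot know the arm that patient would receive. A central service achieves this by keeping the sequence away from the enrolling site. The second paragraph of the concealment section takes that separation away, because it gives generation, enrolment and assignment to one group of authors. This is a statement about roles that the article makes, not a detail left to a fuller document.

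The trial has some room for selection at entry. Most criteria are measurable (AHI, age, BMI, protrusion), but excluding uncooperative patients, or patients with too few teeth to retain the appliance, involves judgement. One appliance is a two-part device on both jaws and the other a hollow plate on the upper jaw, so past assignments are visible to whoever delivers them. The authors also state in advance that they expect the new appliance to do better. If entry decisions were influenced by the coming arm, the groups would differ at baseline in ways that bias the treatment comparison, and with 20 per arm analysis could not reliably remove this.

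**Working it through.** The plan gives no figure on this point to reproduce, so the check has two parts.

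**1. The statements side by side**

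| Question | Concealment section, paragraph 1 | Concealment section, paragraph 2 | Study design |
|---|---|---|---|
| Where does the sequence come from? | Central internet system | Generated by the authors | A computer-generated list that is created |
| Who assigns? | The system, on contact from the site | The authors | Not said; numbers follow order of enrolment |
| Blocks? | Yes, size not given | Not mentioned | Not mentioned |

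Paragraphs 1 and 2 agree only if generation by the authors means no more than setting up the web tool without being able to see its output. The text does not say so. The Study design account can describe the same process, but it does not settle which reading applies.

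**2. What an enrolling author could know**

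*With sight of the sequence:* every upcoming arm, by definition.

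*Without it:* take 1:1 permuted blocks of fixed size 2m, and someone who knows the block size and all past assignments. The best strategy is to guess the arm with more places left in the block. The expected share of correct guesses is

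[m + 2^(2m) / (2·C(2m, m)) − 1/2] / (2m)

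The article gives no block size, so 2, 4 and 6 are assumptions.

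- Block of 2 (m = 1): (1 + 4/4 − 0.5)/2 = 1.5/2 = 0.750
- Block of 4 (m = 2): (2 + 16/12 − 0.5)/4 = 2.833/4 = 0.708
- Block of 6 (m = 3): (3 + 64/40 − 0.5)/6 = 4.1/6 = 0.683

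Enumerating all permuted blocks gives the same values. It also gives 65% for blocks of 10 and 62% for blocks of 20. The share of assignments known with certainty, because one arm is already full within the block, is 50%, 33% and 25% for blocks of 2, 4 and 6, 17% for 10 and 9% for 20. With concealment intact, the guessing rate is 50%.

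For 40 participants, blocks of 2 give 40 × 0.750 = 30 correct guesses and blocks of 4 give 40 × 0.708 = 28.3, against 20 by chance.

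These rates measure how predictable the next arm would be. They do not measure bias in the treatment effect, which would also depend on whether anyone acted on the knowledge.

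**The case against.** The case on the other side has real force on five points.

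- **The order of steps is a safeguard.** The concealment section puts confirmation of eligibility before contact with the system. That stands, and it is much of what is needed. It does not help if the person confirming eligibility already knows the sequence, which the next paragraph leaves open.
- **The authors' role can be read innocently.** The word is plural, no single person is said to fill all three roles, and generating the sequence might mean configuring the web tool. Authors could then enrol and assign without loss of concealment. This is possible, but the text does not say it.
- **A reader might infer that the article gives three incompatible mechanisms, one of them a locally kept list.** The documents do not support that. Study design does not say the list is local, and a web randomiser also works from a computer-generated sequence used in order of enrolment. The clear contradiction lies within the concealment section; Study design adds ambiguity.
- **The guessing rates are conditional.** They need a fixed block size known to the guesser, and the article does not say that blocks are fixed. Leaving the size out of a public article is good practice.
- **A reader might infer that the authors who allocate also score the sleep studies with knowledge of the arm.** The article says only that polysomnography takes place in their department. No scorer is named, and a full protocol could provide for a masked one. Scoring bias is therefore not a shown error.

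Timing also limits the remedy. Trial status gives recruitment from 1 August 2020, twenty participants included by 2 November 2020, and completion expected by 1 June 2021. The article appeared on 16 February 2022.

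**Conclusion.** The point holds as an internal contradiction about who generates, and who can see, the allocation sequence. The section meant to establish concealment names a central system and then gives sequence generation to the group that enrols and assigns. As written, concealment is not secured. To say that it was broken would go too far: if the web system alone held the sequence and released each arm after registration, it was intact.

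The exposure ranges from complete foreknowledge, if an enrolling author could see the sequence, to a correct-guess rate of about 68% to 75% for assumed fixed blocks of 6 down to 2, against 50% by chance. The second figure assumes that the block size and all past assignments are known to the guesser. Neither figure shows that selection took place.

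**What to change.** 1. **State one mechanism in both the Study design and Allocation concealment sections.** The web system generates and holds the sequence, uses varying block sizes undisclosed to enrolling staff, and releases the arm only after the patient is irrevocably registered as eligible.
2. **Remove sequence generation from the enrolling authors' tasks.** If their part was only to configure the tool, say so, and say whether they could view the sequence.
3. **For patients already randomised, report which mechanism was used and who could see the sequence.** On the stated dates, changed system settings may reach few or no patients, so this report and the reconciled text may be the main gain.
4. **As an additional safeguard, code the polysomnography recordings so that the existing scorer does not know arm or visit.** Recordings already scored could be re-scored in the same way.

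The first three steps cost rewording, settings in a tool the article already names, and a short factual report. The fourth costs a small amount of file handling by someone other than the scorer; the article does not describe staffing, so who would do this is for the sponsor to settle. None of the steps changes the sample size, visits or treatment.

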## Intervention

### Mandibular advancement device (MAD) Fig. 2

MAD will be fabricated for the Control Group. An impression of upper and lower jaws will be made for all the participants of this group and will be poured to form a cast. A protrusion index will be recorded using a George Gauge by protruding the mandible to 50% of the maximum protrusion. (roughly 6 mm). The appliance will have an upper and lower part of the elastomer and will be interconnected with a screw that will be tightened by advancing the mandible by 6 mm from its centric position. Symptoms related to temporo-mandibular disorder (TMD) will be evaluated. All the patients will be advised to wear the appliance daily while sleeping at least for 6 h.

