### Exclusion criteria

The patient diagnosed with severe OSAThe patient diagnosed with mild OSAUncooperative SubjectsPatients with severe periodontal diseasesAn edentulous arch, or without a sufficient number of teeth for the adequate retention of the appliance.Patients with temporomandibular joint disordersPatients with pathologic evidence of airway obstruction.Patients with maximal protrusion of less than 6 mm

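### The MAD advancement is given both as 50% of maximum protrusion and as a fixed 6 mm; these agree only at a 12 mm maximum, while eligibility starts at 6 mm

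*Protocol article*

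**What the plan says.** Three statements in the protocol article bear on how far the control device moves the mandible.

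- **Intervention, Mandibular advancement device (MAD), bite registration:** the protrusion index is taken "by protruding the mandible to 50% of the maximum protrusion. (roughly 6 mm"). This is relative to the patient, with an approximate millimetre figure attached.
- **Same paragraph, device assembly:** the screw joining the upper and lower parts is "tightened by advancing the mandible by 6 mm from its centric position". This is an absolute figure, and it is not marked as approximate.
- **Exclusion criteria:** the only criterion on protrusive range is "Patients with maximal protrusion of less than 6 mm". A patient who meets the other criteria is therefore eligible from 6 mm upwards, with no upper limit.

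The setting applies to the whole control arm, described as "group 1 or a control group subjected to MAD (*n*=20"). The article does not require a 12 mm maximum, does not individualise the 6 mm, does not rank the two instructions, and does not give the position from which maximum protrusion is measured.

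**The concern.** A proportional rule and a fixed rule can coincide for only one value of the patient's maximum. Here both are given for the same device in the same paragraph, and the eligibility floor lies well below the value at which they coincide. Someone fitting a MAD to a patient away from that value cannot follow both sentences.

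Advancement is the working principle of the comparator. The Background says that a MAD lowers AHI by holding the mandible forward and downward, which enlarges the airway. The trial's between-group contrast is CMOA against MAD, and the abstract looks ahead to CMOA becoming a gold standard for moderate OSA. A claim of that kind needs a comparator whose setting a reader can state and reproduce.

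There is also a possible tolerability concern. The Background lists tooth pain and temporomandibular joint disorders among reported MAD side effects. Under the fixed instruction, a patient with a small protrusive range could be placed at or near the end of it.

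**Working it through.** **Inputs, all from the protocol article**

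- Relative rule: 50% of maximum protrusion *M*, glossed as about 6 mm (Intervention, MAD).
- Fixed rule: 6 mm from centric position (Intervention, MAD).
- Eligible range: *M* of 6 mm or more (Exclusion criteria).
- Control arm: 20 patients (Study design).

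**Assumption.** *M* is measured from the same centric position as the 6 mm. The article does not say so.

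**Step 1: the plan's own equation of 50% with about 6 mm.** Setting 0.5 × *M* = 6 gives *M* = 6 / 0.5 = 12 mm. The gloss is exact only at 12 mm. It may be meant as an average, but no mean or distribution of *M* is given, so it can be neither reproduced nor refuted in that sense.

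**Step 2: the two rules across the eligible range.** Relative setting = 0.5 × *M*. Fixed setting as a share of maximum = 6 / *M*. Gap = 6 − 0.5 × *M*.

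| Maximum *M* (mm) | 50% rule (mm) | Fixed rule (mm) | Fixed rule as % of maximum | Fixed minus 50% rule (mm) |
|---|---|---|---|---|
| 6 (eligibility floor) | 3 | 6 | 100% | +3 |
| 8 | 4 | 6 | 75% | +2 |
| 10 | 5 | 6 | 60% | +1 |
| 12 | 6 | 6 | 50% | 0 |
| 14 | 7 | 6 | 42.9% | −1 |

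**Step 3: reading the table.** From 6 mm to just under 12 mm, the fixed instruction advances the mandible further than the 50% rule. The two differ by a factor of two at the floor (6 / 3 = 2), where the fixed setting takes up the whole range. Above 12 mm the direction reverses and the fixed instruction advances it less.

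**Step 4: dependence on the assumption.** A different reference point for *M* would change the percentages and move the point of agreement. It would not remove the conflict, because a setting proportional to *M* and a constant setting still meet at a single value of *M*.

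**The case against.** The strongest defence is that the paragraph is one sequential description. On that reading the 50% registration, taken for each patient with a gauge, governs, and the later 6 mm only repeats the approximate figure already given. The article is also a condensed account, and a fuller protocol might say this. The reading is reasonable, but the printed text does not establish it: the screw instruction drops the qualifier and names its own starting position. Nor is this detail merely left out of an article, since the article states both settings and the eligibility limit, and they conflict.

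Three stronger readings are tempting, and the documents do not support them.

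- **That some controls would be set at their full range.** Only a floor on protrusion is stated. Whether any control has a maximum near 6 mm is unknown, and the 100% figure depends on the reference-point assumption. The text supports could, not would.
- **That the amount of advancement drives both the AHI reduction and the jaw side effects.** The Background describes the mechanism and lists side effects, but relates neither to the amount of advancement. The tolerability concern is therefore a possibility, not a demonstrated effect.
- **That the CMOA versus MAD contrast cannot be interpreted.** Randomisation still supports a comparison with MAD as delivered. What is lost is knowledge of which MAD setting was compared, and the ability to reproduce it. Divergent practice between operators is also conjecture, because the article does not describe several people fitting devices.

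The safety side is partly covered: temporomandibular joint disorders are an exclusion, TMD symptoms are evaluated in the MAD arm, and joint and muscle pain are recorded as adverse events. These measures may detect a problem, but they do not define the setting.

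**Conclusion.** The point holds as an internal contradiction in the definition of the comparator. The two stated settings agree at a maximum protrusion of 12 mm and nowhere else, and the eligible range starts at half that value. At the floor they differ by 3 mm, or 50 percentage points of maximum (100% against 50%). At 14 mm they differ by 1 mm in the opposite direction. These percentages rest on maximum protrusion being measured from the same centric position as the 6 mm.

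How many of the 20 controls are affected, and by how much the AHI or adverse event comparison could shift, cannot be worked out from the article. The supported conclusion is that the control setting is not uniquely defined, that this weakens what a CMOA versus MAD result can be taken to mean, and that tolerability in patients with a small protrusive range deserves attention. Which instruction is right is a clinical matter on which this review takes no view.

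**What to change.** 1. The clinical investigators should reconcile the two MAD instructions and the protrusion exclusion criterion into one internally consistent rule, and state the position from which both maximum protrusion and advancement are measured.
2. For every MAD patient, record maximum protrusion (mm) and the setting actually used (mm). The percentage of maximum follows by division.
3. Report the distribution of both, including the percentage of maximum, with the trial results, so that readers can see which comparator was delivered.

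Timing matters. The Trial status section reports twenty participants included by November 2, 2020 and expects recruitment to be complete by June 1, 2021; the article was published in February 2022. A rule for new fittings may therefore come too late, but retrieving and reporting the settings of patients already fitted remains worthwhile.

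The cost is a protocol clarification and two case report form fields. No procedure is added, because applying the exclusion criterion and the 50% registration already requires protrusion to be measured.

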**Fig. 2 Fig2:**
[figure not shown]
Mandibular advancement appliances

### Customized maxillary oral appliance (CMOA)

#### Design (Figs. 3, 4 and 5)

The appliances will have a base plate and an upper plate. The base plate will be adapted to the maxillary hard and soft tissues (teeth and hard palate). This plate will be overextended by 1 mm in the soft palate region to support, lift, and prevent its downfall. The upper plate of the appliance is designed over the base plate, keeping a 2 mm gap between the base plates. This gap will be made hollow. The upper plate will have the occlusal anatomy of the maxillary teeth so that it occludes with the mandibular teeth (in present occlusal relation), but at an increased vertical dimension which will be achieved by hollowing the plate. These hollow maxillary upper plates will have a hole in the anterior region, that is in the central incisor area to promote continuous inflow of the fresh air that will be directed to the posteriors region of the tongue. In addition to this, a bulge will be designed on the palatal surface of the upper plate of the appliance in the posterior region to prevent the backfall of the tongue.

**Fig. 3 Fig3:**
[figure not shown]
Schematic design of modified oral appliance

**Fig. 4 Fig4:**
[figure not shown]
Labeled design of modified oral appliance

**Fig. 5 Fig5:**
[figure not shown]
Prototype of customized maxillary oral appliance

#### Fabrication

Impressions of the upper and lower arch of the second group to be treated with the CMOA will be recorded. The cast obtained from the impression will be scanned for CAD designing with the help of CAD software. The design will be 3D printed in polymethylmethacrylate (PMMA ) material and will be delivered to the patient. All the patients will be advised to wear the appliance daily while sleeping at least for 6 h.

### Investigations

#### Polysomnography (PSG)

An overnight PSG will be performed in the Department of sleep medicine before and after one month and three months of intervention by MAD and CMOA. Recording of PSG will be scored as per the guidelines of the American Academy of Sleep Medicine. The event of apnea or hypopnea per hour will be calculated.

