**Methods:**

A prospective interventional study with a randomized controlled trial will be carried out involving 40 participants (sample size), with an apnea-hypopnea index (AHI) > 15–30, recorded on polysomnography (PSG). Study participants will be randomly divided into the following treatment groups: control group or group subjected to mandibular advancement device (MAD, *n*=20) and second group subjected to customized maxillary oral appliance (CMOA, *n*=20). Baseline assessment of apnea/hypopnea index (AHI), oxygen saturation in blood, percentage of rapid eye movement, electroencephalogram, electrocardiogram, oro-nasal airflow via a pressure transducer, and Epworth Sleepiness Scale will be done. Then both study group participants will receive their respective appliances. And after one month and three months of delivery of the appliance, all the parameters, i.e., AHI, oxygen saturation in blood, percentage of rapid eye movement, electroencephalogram, electrocardiogram, oro-nasal airflow via a pressure transducer, and Epworth Sleepiness Scale will be re-evaluated and compared with the baseline measurements. Descriptive and analytical statistics will be done. SPSS (Statistical Package for Social Sciences) Version 20.1 will be used as statistical software. The statistical significance between the two groups after one month and three months will be evaluated at *p*< 0.05.

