### Outcome measure

#### Primary outcome

The primary outcome will be the change in the score of AHI, SpO2, REM, EEG, ECG, RDI, and ESS from baseline to the end of 1 month of intervention by MAD and CMOA.

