#### Secondary outcome

The change from baseline in the score of AHI, SpO2, REM, EEG, ECG, RDI, and ESS at the end of 3 monthsThe change in the score of AHI, SpO2, REM, EEG, ECG, RDI, and ESS at the end of 1 month and 3 months of intervention

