### Data management/handling with missing data

Data entries undergo an automatic online check for plausibility and consistency. In case of implausibility, 'warnings' will be produced. A responsible investigator will be obliged either to correct the implausible data or to confirm its authenticity and to give an appropriate explanation. If not corrected, the data will be flagged, enabling a convenient check of all questionable entries. A responsible monitor will check all flagged data and generate questions that are sent back to the responsible investigator. The investigator will resolve all “discrepancies.”

Further checks for plausibility, consistency, and completeness of data will be performed after the completion of the study. Queries will be generated based on these checks, combined with a visual control by a responsible monitor/data manager.

All missing data or inconsistencies will be reported back to the sites and clarified by the responsible investigator. If no further corrections are to be made in the trial database it will be declared closed and used for statistical analysis.

For patients with incomplete follow-up, time to last follow-up date will be used as the censoring time in the analysis of time-to-event data. Missing data of continuous outcomes over time will be handled via the multi-level approach making the implicit assumption that data are missing at random, thus not requiring any direct imputation of missing continuous data. The robustness of this assumption will be explored in sensitivity analyses using pattern mixture models assuming that data are not missing at random. Otherwise, no imputation of missing data will be conducted.

In cases of withdrawal, the reason must be recorded and documented. For patients with incomplete follow-up, time to last follow-up date is used as the censoring time in the analysis of time-to-event data.

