### Statistical analysis

The baseline measures before intervention will be compared with the measures obtained after 1 month and 3 months of intervention. Descriptive and analytical statistics will be done. The data will be presented in mean and standard deviations. The normality of data will be tested by the Shapiro-Wilk test. If the data follows normal distribution parametric tests (Independent sample *t*-test and paired *t*-test) will be used and if the data does not follow normal distribution non-parametric tests (Mann-Whitney *U* test and Wilcoxon signed rank test) will be used. The statistical significance will be set at *p*< 0.05. SPSS (Statistical Package for Social Sciences) Version 20.1 (IBM Corporation, Chicago, USA) will be used as statistical software. The inverse probability censoring weighting (IPCW) approach will be done to estimate a treatment effect in the hypothetical scenario.

We expect to confirm the efficacy of the CMOA in managing moderate OSA against MAD by monitoring AHI, SpO2, REM, EEG, ECG, oro-nasal airflow via a pressure transducer, and ESS before and after 1 month and 3 months.

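### The month-1 comparison is fixed as an unadjusted two-sample test, which does not deliver the multi-level handling of missing data stated elsewhere and gives up precision available from the baseline value

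*Protocol article*

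**What the plan says.** Under Polysomnography (PSG): "An overnight PSG will be performed in the Department of sleep medicine before and after one month and three months of intervention". Each patient is therefore due one baseline study and two studies after the appliance is delivered.

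The primary outcome is the "change in the score of AHI, SpO2, REM, EEG, ECG, RDI, and ESS from baseline to the end of 1 month". Month 3 is a secondary outcome: "The change from baseline in the score of AHI, SpO2, REM, EEG, ECG, RDI, and ESS at the end of 3" months. Table 1 makes the same split.

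For the comparison of arms, the Abstract says "The statistical significance between the two groups after one month and three months will be evaluated at" the 0.05 level. The Statistical analysis section says that, for normally distributed data, "parametric tests (Independent sample *t*-test and paired *t*-test) will be used", with Mann-Whitney and Wilcoxon tests otherwise. It names no baseline-adjusted or repeated-measures analysis of the treatment effect.

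The section on data management and missing data says: "Missing data of continuous outcomes over time will be handled via the multi-level approach". It states the missing-at-random assumption, concludes that continuous outcomes need no direct imputation, and plans pattern-mixture sensitivity analyses.

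**The concern.** A multi-level model copes with missing visits because it is fitted jointly to all visits, so a patient with one follow-up value stays in the likelihood. That property belongs to the estimate from the model. It does not carry over to a t-test or Mann-Whitney test on month-1 values, which uses only patients seen at month 1. The article names one method for missing data and another for the comparison, and never says that the CMOA-MAD difference comes from the first.

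Two things are at stake in a trial of 40. A patient who misses the month-1 study drops out of the primary comparison even when a month-3 study exists. And an unadjusted change score uses the baseline value less efficiently than a model with baseline as a covariate, so the interval for the primary contrast is likely to be wider than the same data could give.

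**Working it through.** **Inputs from the article.** 80% power; minimum 16 per group; 20 per group enrolled; significance at 0.05; baseline AHI above 15 and up to 30.

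**Inputs assumed.** Two-sided testing; rho, the correlation of baseline with month 1; r, the correlation of month 1 with month 3; equal variances at all visits unless stated. The article gives no SD, effect size or correlation.

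**The plan's own figure.** With no effect size or SD, 16 per group can only be inverted. Normal approximation: d = (1.960 + 0.842) × √(2/16) = 0.991 SD. With the t distribution, d = 1.024. The enrolled number is consistent with a 20% loss, 16/0.80 = 20, although the article states no rate.

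**Step 1: baseline adjustment, month-1 contrast kept.** With unit variance at each visit:
- unadjusted change: 2(1 − rho)
- baseline-adjusted month-1 value: 1 − rho²
- ratio: (1 − rho²) / [2(1 − rho)] = (1 + rho)/2

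Power is Φ(d√(n/2)/√ratio − 1.960), with d√(16/2) = 2.802 and d√(20/2) = 3.134. The one degree of freedom spent on the covariate is ignored.

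| rho (assumed) | Variance ratio | Power, 16 per arm | Power, 20 per arm |
|---|---|---|---|
| change score as planned | 1.00 | 80% | 87.9% |
| 0.5 | 0.75 | 89.9% | 95.1% |
| 0.7 | 0.85 | 86.0% | 92.5% |

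**Step 2: unequal variances.** Eligibility restricts baseline AHI, so its SD may be smaller than at follow-up. With k = baseline SD / month-1 SD, the ratio is (1 − rho²)/(1 + k² − 2·rho·k). The denominator exceeds the numerator by (k − rho)², so adjustment does not increase the variance, but the gain vanishes when k = rho. For example, rho = 0.5 and k = 0.7 (both assumed) give 0.75/0.79 = 0.95.

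**Step 3: what the second night adds.** With complete data, a repeated-measures model that still targets month 1 gains essentially nothing from month 3. Month 3 helps that contrast only when month 1 is missing, through the correlation between visits. A gain with complete data requires a different target, the average over months 1 and 3. On change scores the variance ratio is then [(1 + r)/2 + 1 − 2·rho]/(2 − 2·rho). At rho = 0.5:

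| r (assumed) | Variance ratio | Power, 16 per arm | Break-even f |
|---|---|---|---|
| 0.5 | 0.75 | 89.9% | 0.73 |
| 0.7 | 0.85 | 86.0% | 0.84 |
| 0.8 | 0.90 | 84.0% | 0.90 |
| 0.9 | 0.95 | 82.0% | 0.95 |

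The power column assumes the same effect at both visits. Break-even f is the month-3 effect as a fraction of the month-1 effect below which averaging loses power: (1 + f)/2 = √ratio, so f = 2√ratio − 1.

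**The case against.** A reader might infer that the trial throws away its month-3 sleep study, or that a month-1 primary is an error. The documents support neither. Month 3 is a named secondary outcome and is tested between groups. A single early timepoint with a later secondary is a legitimate design. Averaging the two visits would answer a different question, so the interval for the protocol's own month-1 contrast is not too wide merely because month 3 is left out of it. The article expects to confirm efficacy by monitoring at both visits, but it does not say the effects are equal. These objections stand, and they are why the point does not rest on averaging.

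It can also be said that the multi-level approach may already be meant for the primary comparison, in which case a patient with only month 3 is kept. That is possible, and a condensed article may leave the model's details elsewhere. But the Statistical analysis section does not leave the comparison open: it names two-sample tests. The two sections still have to be reconciled.

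Finally, the gain cannot be sized from the article. Its correlations and variances are unknown, and with 20 per arm power for the same effect is already 87.9%. That limits the size of the point but does not remove the conflict.

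**Conclusion.** The point holds as an inconsistency between two sections, with a moderate and avoidable loss of precision. The stated handling of missing continuous data requires the treatment effect to come from the multi-level model, and the named tests do not provide that.

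For the unchanged month-1 contrast, baseline adjustment would cut the variance by 25% at rho 0.5 or 15% at rho 0.7, given equal variances and a roughly linear relation with baseline. The cut could be much smaller if baseline AHI varies less than follow-up AHI. The further benefit from keeping patients with only one follow-up study depends on how many there are, which the article cannot tell us; a patient lost at both visits adds no follow-up information under either analysis.

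The separate gain from averaging the two visits ranges from substantial to about two percentage points of power, and can turn into a loss if the effect fades. It is not a reason to replace the primary target.

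**What to change.** In the Statistical analysis section, estimate the CMOA-MAD difference in AHI and the other continuous PSG outcomes from one repeated-measures (multi-level) model with arm, visit, arm-by-visit and baseline value. Include every patient with at least one follow-up sleep study. Keep the stated target, "from baseline to the end of 1 month of intervention by MAD and CMOA", as the primary contrast, and report the month-3 contrast from the same model, each with a 95% confidence interval. State that this is the model to which the missing-at-random statement and the pattern-mixture sensitivity analyses refer. The two-sample tests can remain as supportive analyses.

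If the average over months 1 and 3 is of interest, add it as an optional or supportive contrast, described as a different estimand.

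This needs no extra patients, visits or sleep studies. It does need attention to timing: recruitment began in August 2020 and 20 of 40 patients were included by November 2020. If the change counts as substantial, the article's own amendment section requires a signed amendment and approval before implementation. Keeping the month-1 target limits the change to the method of analysis. It should be dated and locked before any data are compared by arm.
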